### Data collection and management

The data will be collected according to the primary and secondary endpoints at the time points, and using the methods, described above. All the data will be deposited safely in the in-built server in Huadong Hospital with full confidentiality. Participants in this study will be referred to by a code which differs from their true name. Procedures for data management will be approved by the trial manager and other clinicians before the first participant is enrolled.

### Statistical analysis

The impact of prolonged LPP and SPP on myocardial injury after robot-assisted urological surgery will be evaluated by comparing the changes in the patients with TnT levels of 0.01 or lower. A *t* test or a Fisher’s exact test will be performed as appropriate. The homogeneity of the data collected from the two hospitals will be assessed using the Mantel-Haenszel test. The impact will further be investigated by varying the TnT cutoff, and by examining the effects of CAD and its interaction effect with the main treatment (SP/LP); some other covariates will be justified using a logistic regression model. The distributions of the TnT levels measured at different times will be estimated and the distributional differences will be evaluated between the patients treated with LP and SP, respectively. In addition, the association between the TnT levels measured at T0, T1, T2, T3 and T4 (the peak TnT levels measured at 24 h after surgery) will be assessed. Receiving Operating Characteristic (ROC) curves will be used to assess the value of using the high-sensitivity TnT assays for early detection of elevated TnT levels among patients treated with LP and SP, respectively. The impact of LPP and SPP on pulmonary mechanics and oxidative stress at difference time points will be evaluated using regression analysis, with the effects of CAD and other covariates justified. A statistical analysis plan will be drafted and approved before unlocking the dataset.

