To lower the impact of pneumoperitoneum on myocardial physiological status while providing appropriate space for operation, low-pressure pneumoperitoneum (LPP) at a range of 7–10 mmHg is considered optimum by surgeons. Numerous clinical trials have been done to compare LPP with SPP in laparoscopic cholecystectomy, the duration of which is often under 2 h [21]. A high IAP pneumoperitoneum was found to be associated with more fluctuations in hemodynamic parameters and increased peritoneal absorption of CO_2_ as compared to LPP in laparoscopic cholecystectomy [22]. Cardiac electrophysiological analysis showed that LPP results in lower sympathetic activation than SPP [23]. Prolongation of corrected QT dispersion (QTcd), which is associated with cardiovascular morbidity and mortality, was significantly higher in the high-pressure pneumoperitoneum group (15 mmHg) than in the LPP group (7 mmHg) [24]. In addition, a study focusing on solid intra-abdominal-organ flow suggested that increased intraperitoneal pressure substantially reduced the portal venous flow as compared with lower IAP [25]. A randomized controlled trial conducted by Kanwer et al. showed that LPP used in laparoscopic cholecystectomy benefited patients by lowering postoperative pain intensity [25, 26]. Hua et al. performed a meta-analysis in 2013 and showed that LPP was feasible and safe, resulted in reduced postoperative pain and nearly the same operative time as SPP [26, 27]. Prolonged robot-assisted surgery normally takes 4–5 h, sometimes 7–8 h, which is much longer than the time taken for cholecystectomy. Thus the outcome might be different, due to the different lengths of surgical time. So far, there are few studies concerning the comparison of LPP and SPP on myocardial injury after prolonged robot-assisted urological surgery. Postoperative myocardial injury after noncardiac surgery (MINS) has been proved to be an independent predictor of 30-day mortality [28]. An elevated troponin T (TnT) level after noncardiac surgery, irrespective of the presence of an ischemic feature, independently predicted 30-day mortality. A peak TnT level of 0.03 ng/mL or greater was used as diagnostic criterion for MINS in a cohort study reported in 2014 [29]. The N-terminal of the prohormone brain natriuretic peptide (Nt-proBNP) is an indicator for cardiac failure and is being used in routine tests in the emergency room [30]. It has been demonstrated that peak Nt-proBNP levels at peak IAP were correlated positively with indexes of cardiac afterload (systemic vascular resistance (SVR) and peripheral vascular resistance (PVR)). A strongly negative correlation between Nt-proBNP levels and cardiac output at peak IAP was also reported [31].

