### Primary endpoint

The troponin T level is set as the primary endpoint for this trial to evaluate myocardial injury, and this will be measured for each patient who will undergo prolonged robot-assisted urologic surgery at the following four time points: Ta (2 to 3 h after surgery), Tb (6 h after surgery), Tc (12 h after surgery) and Td (24 h after surgery) using the fifth-generation high-sensitivity TnT assay.

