### Sample size calculation

Based on the summary statistics for the troponin T (TnT) values [29, 32], we use a peak TnT level of 0.01 ng/mL or less as the reference group, and to compute the sample sizes. With 140 patients in each of the two treatment groups, the power will be at least 0.70 to detect an increment of 80 % of patients with a TnT level of 0.02 or higher. The total sample size will be 280, which will ensure the detection of differences of certain pre and perioperative respiratory parameter levels (with power of at least 0.85) [33]. The number of enrolled patients in each center is 140, and the allocation ratio for the two groups is 1:1.

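### The trial is powered on TnT of 0.02 or higher, but the main comparison is stated for TnT of 0.01 or lower, so the stated power does not belong to the stated analysis

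*Protocol article*

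**What the plan says.** Three sections of the protocol article describe the primary quantity.

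- **Primary endpoint:** "The troponin T level is set as the primary endpoint for this trial to evaluate myocardial injury". It is measured at Ta, Tb, Tc and Td, up to 24 h after surgery. No peak, single time or cut-off is named.
- **Sample size calculation:** "we use a peak TnT level of 0.01 ng/mL or less as the reference group". With 140 patients per group, power is at least 0.70 "to detect an increment of 80 % of patients with a TnT level of 0.02 or higher". No base rate or alpha is given.
- **Statistical analysis:** the impact of the two pressures "will be evaluated by comparing the changes in the patients with TnT levels of 0.01 or lower", by a t test or Fisher's exact test, whichever is appropriate. The value 0.02 does not appear in this section. It then adds: "The impact will further be investigated by varying the TnT cutoff".

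The same section promises that an analysis plan will be approved before the dataset is unlocked. The Trial status section says that inclusion has not yet started.

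**The concern.** The sample size section fixes an event and attaches a power to it. The analysis section then states a main comparison that does not use that event. An analysis plan written later could not follow both and would have to overrule one of them.

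Two things are at stake. First, the only justification for 280 patients refers to a quantity that the analysis section does not test. Second, the wording of the main comparison can be followed literally. In that case patients with raised TnT, the ones in whom the trial expects to see harm, would be left out, and the arms would be compared in groups no longer protected by randomisation.

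**Working it through.** **1. The stated power.** Inputs from the document: 140 per arm, 1:1 allocation, an 80% increment, power at least 0.70. Assumed, because not stated: two-sided alpha 0.05, and the increment read as a rate ratio of 1.8. An absolute rise of 80 percentage points gives power of about 1.0, which does not fit the stated 0.70.

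Normal approximation, with p2 = 1.8 × p1 and p̄ their mean:

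power = Φ{ [ (p2 − p1) − 1.96 × √(2p̄(1 − p̄)/n) ] / √[ (p1(1 − p1) + p2(1 − p2))/n ] }

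At p1 = 0.15: p2 = 0.27, p̄ = 0.21, and the two standard errors are 0.0487 and 0.0482. So power = Φ[(0.12 − 0.0954)/0.0482] = Φ(0.51) = 0.695.

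| Base rate at ≥0.02 | Normal approximation | Fisher's exact test (exact power) |
|---|---|---|
| 5% | 0.258 | – |
| 10% | 0.488 | 0.425 |
| 15% | 0.695 | 0.648 |
| 16% | – | 0.689 |
| 17% | – | 0.726 |
| 20% | 0.850 | – |

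The stated 0.70 can be recovered at a base rate of about 15.1% by the normal approximation, or about 16–17% with Fisher's test. It cannot be confirmed, because the base rate is not given. In every case it is a power for the event at 0.02 or higher.

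**2. Three readings of the analysis sentence.**

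- *Restriction.* The arms are compared among patients at 0.01 or lower. The sample size section defines that category by peak TnT, so membership is decided after randomisation and by the outcome itself.
- *Proportion.* The share of patients at 0.01 or lower is compared. All patients count, but a value between 0.01 and 0.02 is a failure here and a non-event in the powered comparison.
- *Baseline.* Patients with preoperative TnT of 0.01 or lower are compared. This does not condition on the outcome, but the sentence then names no outcome. The Primary endpoint section lists no preoperative measurement, and the inclusion criterion asks only for a normal value.

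None of the three is the event in the sample size section.

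**3. How far the readings differ.** This step is illustrative. Assumptions: lognormal TnT, 15% (low pressure) versus 27% (standard pressure) at 0.02 or higher, log-SD of 0.5, 0.8 or 1.1.

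P(TnT ≤ 0.01) = Φ(z − ln 2/SD), with z = 1.036 for low pressure and 0.613 for standard pressure. At SD 0.8, ln 2/SD = 0.866, so the shares are Φ(0.170) = 0.57 and Φ(−0.254) = 0.40. The low-pressure share between the cut-offs is 0.85 − 0.57 = 0.28. The restriction drops 1 − (0.57 + 0.40)/2 = 52% of patients.

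| | SD 0.5 | SD 0.8 | SD 1.1 |
|---|---|---|---|
| At ≤0.01, low vs standard | 36% vs 22% | 57% vs 40% | 66% vs 49% |
| Low-pressure arm between 0.01 and 0.02 | 49% | 28% | 19% |
| Dropped by the restriction | 71% | 52% | 42% |
| Power, t test of log TnT, all patients | 0.93 | 0.95 | 0.94 |
| Power, t test of log TnT, only ≤0.01 | 0.13 | 0.30 | 0.39 |
| Power, Fisher at ≤0.01, all patients | 0.70 | 0.76 | 0.76 |
| Power, Fisher at ≥0.02, all patients | 0.64 | 0.63 | 0.67 |

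The powers come from 1,500 simulated trials per column. The last row varies only by simulation error, since the rates are the same in each column (exact value 0.648). The restricted t test recovers 0.054/0.212 = 25%, 0.122/0.339 = 36% and 0.192/0.466 = 41% of the true log difference.

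The 80% increment does not carry over to the other cut-off either. At SD 0.8 the shares above 0.01 are 43% and 60%, a ratio of about 1.4, not 1.8.

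**4. The test.** A t test compares mean levels and Fisher's test compares proportions. They address different estimands, so leaving the choice open leaves the primary estimand open as well.

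**The case against.** The strongest reply is that the literal reading is not the likely one. Varying a cut-off, using Fisher's test and fitting a logistic model all point to a yes/no outcome split at 0.01, and the sample size section treats 0.01 or less as a category. On that reading every randomised patient is kept, and under the assumptions above power is no worse than at 0.02 (0.70 to 0.76 against 0.63 to 0.67). This stands. The low power of the restricted test is a consequence of following the sentence as worded, not a forecast. The mismatch remains, because the powered event is still a different one.

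Three stronger inferences are tempting, and the document does not support them.

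- *The primary test can be picked after seeing the data.* The Statistical analysis section promises an approved plan before the dataset is unlocked and presents other cut-offs as further investigation.
- *The 0.03 criterion is a further primary quantity.* The Background says only that it "was used as diagnostic criterion for MINS in a cohort study". The trial does not adopt it.
- *Values between 0.01 and 0.02 are certain to occur.* The Primary endpoint section says that TnT is measured "using the fifth-generation high-sensitivity TnT assay" but gives no reporting step. If results were recorded only to 0.01, the two categories would be complements. A single split at either value also classifies everyone. The gap arises only when the two definitions are combined.

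**Conclusion.** The point holds as a contradiction between stated passages. The power of at least 0.70 is attached to TnT of 0.02 or higher. The main comparison is stated for TnT of 0.01 or lower, and the endpoint section names neither a cut-off nor a summary. Because the protocol positively states both comparisons, this is not detail left to the analysis plan.

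The size depends on the reading. If the sentence is followed literally, the comparison is within an outcome-defined subset, with power of about 0.13 to 0.39 in the illustration. If it is a proportion at 0.01 or lower, there is no power loss, but the event is different and its power is unstated. The lognormal shape, the 15% and 27% rates, the rate ratio of 1.8 and the two-sided 0.05 are all assumptions. The conflict between the sections depends on none of them.

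**What to change.** Define one primary endpoint in all randomised patients and use it in identical words in the Primary endpoint, Sample size calculation and Statistical analysis sections.

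- Name the summary, for example peak TnT as the maximum over Ta to Td.
- Use one threshold without a gap. Splitting at 0.02 or higher versus below 0.02 keeps the event already powered.
- Name the matching test: Fisher's exact test for this binary endpoint.
- Delete the restriction to patients at 0.01 or lower.
- Label other cut-offs and single time points as supportive.
- Restate the power for the chosen endpoint, with its base rate, alpha and sidedness, and say that the 80% is a relative increase if that is what is meant.

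The cost is rewording plus one recalculation before enrolment. The stated power may change. With Fisher's test at a ratio of 1.8 and two-sided 0.05, 140 per arm gives 0.425 at a base rate of 10% and 0.648 at 15%, and reaches 0.70 only from about 16–17%. If the base rate is lower, the sponsor would have to accept lower power or revisit the sample size.

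### Fisher's exact test for the TnT proportions is valid but conservative at 140 per arm; Boschloo's exact test keeps the 5% limit and gains up to about 4.5 points of power

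*Protocol article*

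**What the plan says.** The Statistical analysis section evaluates the treatment effect by "comparing the changes in the patients with TnT levels of 0.01 or lower". It names a t test or Fisher's exact test for this: "Fisher’s exact test will be performed as appropriate". The Mantel-Haenszel test is assigned to homogeneity between the two hospitals, and logistic regression to covariates and the CAD interaction. Fisher's is thus the only unadjusted test named for a between-arm proportion.

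The Sample size calculation section also works with a proportion. Its target effect is worded "to detect an increment of 80 % of patients with a TnT level of 0.02 or higher", and on power for that target the section says "With 140 patients in each of the two treatment groups, the power will be at least 0.70". It fixes the design ("The total sample size will be 280"; "the allocation ratio for the two groups is 1:1") but gives no base rate, no alpha, no sidedness and no test for the 0.70. The article says that a statistical analysis plan will be approved before the dataset is unlocked.

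**The concern.** Fisher's test conditions on both margins of the 2×2 table. The conditional distribution is discrete, so the test usually cannot use its full nominal level, and its error rate over repeated trials is below 5%. Power is lost with it. At 140 per arm this is avoidable: an unconditional exact test gives the same guarantee and uses more of the 5%.

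The loss matters more than usual here because the trial accepts a power of only 0.70 for its target effect. The power statement also does not say which test it refers to, so a reader cannot tell whether the test named in the analysis section delivers it.

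**Working it through.** **Inputs.** From the article: 140 per arm, 1:1 allocation, power of at least 0.70, and an 80% increment in the proportion with TnT of 0.02 or higher. Assumed: two-sided 5%; a range of base rates p; and the increment read as p versus 1.8p. An absolute increment of 80 percentage points would give power of about 1 (10% v 90%, for example), so it cannot be what 0.70 refers to.

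**1. The plan's own figure.** It cannot be strictly reproduced, because base rate and alpha are missing. One can only solve for the base rate that would give 0.70. The usual two-proportion formula is

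power = Φ[(p₂ − p₁ − 1.96·s₀)/s₁], with s₀ = √(2·p̄(1−p̄)/n) and s₁ = √((p₁(1−p₁) + p₂(1−p₂))/n).

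With p₁ = 0.151, p₂ = 0.272 and n = 140: p̄ = 0.2115, s₀ = 0.0488, s₁ = 0.0483, and the power is Φ[(0.121 − 0.0957)/0.0483] = 0.70. If Fisher's test itself was powered by exact calculation, 0.70 needs about 16.3% v 29.3%.

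**2. True size.** Over all 141 × 141 possible outcomes,

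size(π) = Σₓ Σᵧ b(x; 140, π)·b(y; 140, π)·1[reject],

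where b is the binomial probability and π the common event rate. Fisher's test rejects when its two-sided p is at most 0.05. Boschloo's test uses the Fisher p as its statistic and rejects at or below the largest cut-off that keeps size(π) ≤ 0.05 for every π. At 140 per arm that cut-off is 0.0638.

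| Common rate | Fisher | Boschloo |
|---|---|---|
| 5% | 2.3% | 3.4% |
| 10% | 3.2% | 4.2% |
| 15% | 3.3% | 4.4% |
| 20% | 3.5% | 4.6% |
| 25% | 3.7% | 4.8% |
| Maximum over all rates | 3.85% | 4.94% |

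Fisher's size falls below 2% only at common rates under about 3.7%. Because 0.0638 exceeds 0.05, every table that Fisher's test rejects is also rejected by Boschloo's; the enumeration found no exception.

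**3. Power for p v 1.8p**, from the same sum with two different rates:

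| p v 1.8p | Fisher | Boschloo | Gain (points) |
|---|---|---|---|
| 5% v 9% | 0.1844 | 0.2170 | 3.3 |
| 8% v 14.4% | 0.3329 | 0.3746 | 4.2 |
| 10% v 18% | 0.4250 | 0.4675 | 4.3 |
| 12% v 21.6% | 0.5151 | 0.5605 | 4.5 |
| 15.1% v 27.2% | 0.653 | 0.694 | 4.1 |
| 16.3% v 29.3% | 0.7002 | 0.7381 | 3.8 |
| 17% v 30.6% | 0.7259 | 0.7618 | 3.6 |
| 20% v 36% | 0.8205 | 0.8477 | 2.7 |
| 25% v 45% | 0.9291 | 0.9429 | 1.4 |
| 30% v 54% | 0.9784 | 0.9834 | 0.5 |

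**4. Sensitivity to the assumed alpha.** At one-sided 5%, Fisher's maximum size is 4.1%, and the gain at 12% v 21.6% is 0.6733 − 0.6432, or 3.0 points.

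**5. Uncorrected chi-square.** Its maximum size by the same enumeration is 5.14%, so it does not carry the 5% guarantee.

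**The case against.** The strongest reply is that nothing is wrong. Fisher's test controls type I error, and whether a 2×2 test should be judged conditionally or unconditionally is an old methodological choice. The wording is also permissive: it allows a t test and says as appropriate, and a later analysis plan could name another exact test. Part of this stands. The point concerns efficiency, and it applies only where TnT is analysed as a proportion. But the cutoff in the analysis section and the power statement both point to a proportion, and Fisher's test applied as written has the lower power.

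Two stronger readings are tempting, and the article supports neither.

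- *The named test fails to deliver the stated 0.70.* This follows only if the 0.70 came from the two-proportion formula; Fisher's test then gives about 0.65. If the sponsor powered on Fisher's test, 16.3% v 29.3% gives 0.700 and there is no shortfall. The text favours neither origin.
- *About 14 patients per arm are thrown away.* The formula gives Fisher's 0.653 at about 126 per arm, and 140 − 126 = 14. But that sets an exact power against an approximate formula, not against the proposed test. On the same formula Boschloo's 0.694 corresponds to about 138 per arm, so the difference is about 12, and no patient's data are discarded.

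Two further reservations also stand. The analysis section uses a cutoff of 0.01 and the power statement 0.02; until these are reconciled the relevant base rate, and so the exact gain, is unknown. And Boschloo's test in its plain form, like Fisher's, ignores centre.

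**Conclusion.** The point holds as a worthwhile efficiency improvement, not as an error of validity. At 140 per arm and nominal two-sided 5%, Fisher's test works at a true level of about 2–4% (maximum 3.85%). Boschloo's test never exceeds 4.94% and is never less powerful. The gain for a 1.8-fold ratio is about 4 points at base rates of roughly 8–17%, which include those that would yield the stated 0.70. It shrinks to 0.5 points at 30%. Whichever way the 0.70 arose, the change helps: about 0.65 becomes about 0.69 if it came from the formula, and 0.70 becomes about 0.74 if it was computed for Fisher's test.

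The conclusion rests on the assumed two-sided 5% level, the assumed base rates, the reading of the increment as a ratio, and TnT being compared as a proportion.

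**What to change.** In the Statistical analysis section, name Boschloo's unconditional exact test in place of Fisher's for the unadjusted comparison of TnT proportions. Do not list the uncorrected chi-square test as an equivalent, since its size can exceed 5%.

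In the Sample size calculation section, state the base rate, alpha (with sidedness) and test behind the 0.70, and recompute the power for the test that will be used.

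The cost is a short edit to each section and one recalculation, carried into the analysis plan before the dataset is unlocked. It needs no additional patients, measurements or data, and the 5% limit on type I error is kept.

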## Discussion

Prolonged robot-assisted urological surgery in the Trendelenburg position may include several risk factors that can affect cardiopulmonary physiological status. Our study is designed to investigate the effects of different IAPs on myocardial injury. Physiological changes caused by CO_2_ pneumoperitoneum are complicated, may consist of an intra-abdominal mechanical compressive effect, neurohumoral responses and changes induced by the systemic absorption of CO_2_ [34]. Although previous studies have focused on hemodynamic performance during prolonged robot-assisted surgeries in the Trendelenburg position, few have paid close attention to potential subclinical myocardial injury after different pneumoperitoneal pressures, which may be highly relevant to postoperative mortality.

To our knowledge, the adverse effects caused by utilizing pneumoperitoneum include mechanical compression effects: systemic vascular resistance (SVR), mean arterial pressure (MAP), cerebral blood flow (CBF) and intracranial pressure (ICP) will be increased [35, 36]. On the other hand, renal blood flow (RBF), portal blood flow, splanchnic blood flow and pulmonary compliance will be decreased [37–39].

Additionally, significant hypercapnia and acidosis may occur due to CO_2_ absorption. Hypercapnia may cause a decrease in myocardial contractility. Vasopressin, renin, aldosterone and catecholamine levels also increase sharply after CO_2_ pneumoperitoneum is established [40], with their consequent metabolic and hemodynamic effects.

The Trendelenburg position required by the prolonged robot-assisted urological surgery may cause increased venous return and decreased lung compliance, thus affecting cardiopulmonary function [25, 28, 29]. It commonly causes decreased functional residual capacity (FRC) and decreased pulmonary compliance, increased pulmonary wedge pressure, increased cardiac volume, and normalizing of cardiac afterload while increasing preload. To rule out the inaccuracies caused by changing the angle of the Trendelenburg position, a method to guarantee a fixed angle (30° in this study) is essential. In this trial, we employ a smartphone app to ensure achieving a constant angle for the Trendelenburg position. Once calibrated, the same smartphone will be used for all the patients enrolled. This makes the angle adjustment more convenient and the outcomes more reliable.

Other rare complications of pneumoperitoneum include pneumothorax, inadvertent gas embolism, vascular injury and inadvertent extraperitoneal insufflation.

As described above, the pneumoperitoneal physiology in the Trendelenburg position is intricate. We aim to protect the patients from injury by careful preoperative examination, so that undiagnosed conditions can be identified and pretreated. Standard intraoperative monitoring will be used for all patients, and invasive hemodynamic monitoring (Vigileo with the FloTrac system) will be used to monitor the cardiovascular response to pneumoperitoneum and position changes. ETCO_2_ and airway pressure are commonly assessed to assure adequacy of ventilation and blood gas analysis will be conducted when necessary. Other rare complications will be appropriately treated as soon as they are detected.

Data attrition of the clinical trial would affect the validity of our results markedly. In this study, approaches will be adopted to minimize any impact this may bring. The designed follow-up period of this study is only 24 h post surgery, so it is unlikely that the patients who meet the inclusion criteria would drop out, which is confirmed by the ongoing preliminary trial. Besides, we have the capability for a rapid response to any perioperative emergency events. If attrition does occur, we will carefully discuss the reasons and estimate the impact on the trial. If it is not a source of bias we will employ the complete-case method, where the missing data will be excluded from the analysis. As we have a population large enough to complete the trial in the designated period, this is believed to be the simplest and most efficient method for our study.

The main limitation of this trial is the inevitable bias in age and sex distribution of the enrolled patients. Although the age range in the inclusion criteria is set at 18–80 years, most patients requiring urological surgery, especially resection, are middle-aged and elderly men. Thus the conclusion drawn by this study might be not applicable to female patients and cases in different age groups.

As the trial designed in this study is bicenter, the bias caused by the differences in execution between centers and patient preference of hospital selection might be a challenge. Both the hospitals participating in this trial are tertiary referral centers in Shanghai, but located over 20 km apart and there is an existing long-term collaboration between the two hospitals, which is the basis of this study. From the past years’ patient baseline data, there is no significant competitive recruitment or imbalance between the two hospitals. Thus it could be supposed that the potential bias of those enrolled would not markedly affect the outcome of this study. However, to eliminate any bias caused by variability in anesthesiologists’ abilities, regular meetings and training for clinicians participating in this clinical trial will be ongoing and continued into the future.

